**Methods/Design:**

This paper presents the protocol of a prospective, single-blinded, multicenter cluster randomized controlled trial. In total, 200 patients with OA of the hip and/or knee will be randomly allocated into either e-Exercise or usual care (physical therapy). E-Exercise is a 12-week intervention, consisting of maximum five face-to-face physical therapy contacts supplemented with a web-based program. The web-based program contains assignments to gradually increase patients’ physical activity, strength and stability exercises and information about OA related topics. Primary outcomes are physical activity and physical functioning. Secondary outcomes are health related quality of life, self-perceived effect, pain, tiredness and self-efficacy. All measurements will be performed at baseline, 3 and 12 months after inclusion. Retrospective cost questionnaires will be sent at 3, 6, 9 and 12 months and used for the cost-effectiveness and cost-utility analysis.

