Up till now, previous research in web-based interventions has focused on interventions without human support. Unfortunately, the effects of these interventions are small, especially in the long-term [20–24]. These modest effects can partly be explained by the absence of personal guidance [17]. To illustrate, in the study by Bossen et al. [23], patients cited that the lack of face-to-face contact in a self-guided web-based intervention was an important reason to discontinue. Hence, the combination of a web-based intervention with face-to-face contact has been recommended by several researchers [20, 25, 26]. To date, there are no studies investigating the (cost)-effectiveness of a blended intervention in the physical therapy setting. Therefore, we have developed e-Exercise and have planned to evaluate and implement this blended intervention. The intervention will be based on the Dutch “KNGF guideline OA hip-knee” for physical therapists [10]. The web-based part will be an adapted version of the previously developed and evaluated online PA program Join2Move [24], a web-based intervention for OA patients without support of a physical therapist. The aim of this study is to determine the (cost)-effectiveness of e-Exercise compared to usual care (physical therapy). Our first hypothesis is that e-Exercise will be more effective in terms of increasing PA and improving physical functioning in patients with hip and/or knee OA as compared to usual care. The second hypothesis is that e-Exercise will be cost-effective in comparison to usual care by physical therapists. The research question of this RCT study is: What is the short- (3 months) and long-term (12 months) (cost)-effectiveness of e-Exercise in patients with hip and/or knee OA on PA and physical functioning in comparison to usual care?

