### Measurements

Three online questionnaires (0, 3 and 12 months) will be used for data collection. Participants will receive an accelerometer for the measurement of objective PA (0, 3 and 12 months). The physical therapists will measure physical functioning objectively at baseline and post-treatment (3 months). In addition, online cost questionnaires will be sent (0, 3, 6, 9 and 12 months). We offer no financial incentives to complete questionnaires or to wear accelerometers. Table 2 gives a summary of all measures that will be collected.

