### Sample size

The power calculation is based on a previous multicenter cluster RCT study among patients with hip and/or knee OA [27] and performed for the primary outcome measure physical functioning (power 0.8; alpha 0.05). In this current RCT study, the target sample size will be 200 participants to detect a small to medium effect size (0.2-0.4) in physical functioning at a 2-sided significance level of 0.05 and anticipating on maximum loss to follow up of 20%.

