### Statistical analysis

Descriptive statistics will be used to describe the main characteristics of the study population and to explore baseline comparability (frequencies, t-test, Chi-square). Primary baseline variables between the response and the non-response group will be performed in order to investigate selective attrition. The primary analysis will be performed according to the intention-to-treat principle. In addition, per-protocol analyses that include only adherent patients of the intervention group and the entire control group will be performed. For all analyses, a two-tailed significance level of p < 0.05 is considered to be statistically significant. All analyses will be carried out with the statistical package STATA.

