Although the study is well-considered, we take into account potential operational issues. First challenge is the recruitment of sufficient numbers of physical therapists. Since e-Exercise is characterized by fewer physical therapy sessions, physical therapists will receive less reimbursement from health insurances compared to usual care. To deal with this challenge, accreditation points for participating physical therapists will be supplied in order to make study participation more attractive. Another incentive is that physical therapists keep their access to the website after the study is finished. The second challenge is the non-usage of the web-based part of e-Exercise. Previous studies have indicated that participants in online interventions are less motivated and feel less pressure to continue compared to traditional face-to-face interventions [59]. However, in order to stimulate website usage, we will incorporate email reminders into the program. But most importantly, since this study concerns a blended intervention, which is a combination of face-to-face contact with e-health, e-Exercise is expected to maximize adherence compared to self-guided internet interventions [17, 23].

There are several strengths in the design of this study. First, we elaborate on the study results of Joint2Move [24]. This intervention showed to be an effective web-based intervention for patients with OA of the hip and/or knee and will be the fundament for e-Exercise. Second, the primary outcome measurements PA and physical functioning will be measured subjectively (questionnaires) and objectively by means of accelerometers and the timed “Up & Go test”. Third, the 12-month follow-up will result in data about long-term effectiveness. The last strength is that e-Exercise will be evaluated in daily physical therapy practice, the setting in which the intervention will be implemented after the presented trial. Therefore, user experiences can be used in order to improve e-Exercise and to facilitate implementation.

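### Seven unranked primary comparisons, each tested at two-sided 0.05 with no adjustment or success rule, leave the error rate of the effectiveness claim uncontrolled

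*Protocol article*

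**What the plan says.** The abstract names two constructs side by side: "Primary outcomes are physical activity and physical functioning". Table 2 and the section Primary outcome measures give each construct one self-reported and one objective instrument. Physical functioning has the HOOS and/or KOOS daily-living subscale and the Timed Up & Go. Physical activity has the SQUASH and the ActiGraph accelerometer. The Discussion presents this pairing as a strength: "the primary outcome measurements PA and physical functioning will be measured subjectively (questionnaires) and objectively by means of accelerometers", with the Timed Up & Go named alongside.

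The follow-up times are set under Measurements:

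- Questionnaires: "Three online questionnaires (0, 3 and 12 months) will be used for data collection".
- Accelerometer: "Participants will receive an accelerometer for the measurement of objective PA (0, 3 and 12 months").
- Timed Up & Go: "The physical therapists will measure physical functioning objectively at baseline and post-treatment (3 months").

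Both horizons belong to the research question: "What is the short- (3 months) and long-term (12 months) (cost)-effectiveness of e-Exercise in patients with hip and/or knee OA on PA and physical functioning". The Effectiveness section likewise estimates a short-term and a long-term effect and puts neither first.

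The decision threshold is general: "For all analyses, a two-tailed significance level of p < 0.05 is considered to be statistically significant". The sample size was "performed for the primary outcome measure physical functioning (power 0.8; alpha 0.05"), with no instrument or time point named.

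**The concern.** The first hypothesis is one of superiority: e-Exercise should raise physical activity and improve functioning more than usual care does. The article supplies seven primary tests of it, each at the full 5%, and does not say which of them decides. A favourable finding on one instrument at one visit could then be reported as a positive trial although the other six show nothing.

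Disagreement among the instruments is quite possible. The SQUASH asks about a normal week over recent months, while the accelerometer covers five days. The Timed Up & Go is timed by therapists who know the allocation, and it has no 12-month value. If these results diverge, the article does not say what the trial has shown. The same gap reaches the Economic evaluation section, where the cost-effectiveness ratio divides by the difference in activity and functioning with no instrument specified.

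**Working it through.** **Plan's own figure.** The article states no error rate for the set of primary tests, so there is none to reproduce. The sample size of 200 concerns power for functioning and does not enter this check.

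**Step 1: count the contrasts** (Table 2 and Measurements). HOOS/KOOS is counted once, because the joint determines the form.

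| Measure | Follow-ups | Contrasts |
|---|---|---|
| HOOS/KOOS function | 3, 12 months | 2 |
| Timed Up & Go | 3 months | 1 |
| SQUASH | 3, 12 months | 2 |
| Accelerometer | 3, 12 months | 2 |
| Total | | 7 |

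**Step 2: independent tests, no true effect anywhere, any one result counting.**

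- Any significant difference, either direction: 1 − 0.95^7 = 0.302, or 30.2%.
- A significant difference favouring e-Exercise (upper 2.5% of each test): 1 − 0.975^7 = 0.162, or 16.2%.
- For one two-sided test the corresponding figures are 5% and 2.5%.

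**Step 3: correlated tests.** The article gives no correlations, so these are assumptions. Each triple is (same measure at 3 and 12 months; two measures of one construct at the same visit; measures of different constructs at the same visit). For different measures at different visits, the between-measure value is multiplied by the first number. The test statistics were simulated as multivariate normal with 1,000,000 draws, with simulation error of about 0.1 percentage point.

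| Assumed correlations | Either direction | Favouring e-Exercise |
|---|---|---|
| 0.5; 0.3; 0.1 | 27.9% | 14.4% |
| 0.6; 0.4; 0.2 | 26.4% | 13.5% |
| 0.7; 0.5; 0.3 | 24.4% | 12.3% |
| 0.8; 0.6; 0.4 | 21.9% | 11.0% |
| 0.8; 0.6; 0.4, no reduction across visits | 21.3% | 10.6% |

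The ranges are therefore about 21–28% and about 11–14%.

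**Step 4: other readings, independent tests.**

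- 3 months and 12 months as separate families. Four tests at 3 months: 1 − 0.95^4 = 18.5% either direction, 1 − 0.975^4 = 9.6% favourable. Three tests at 12 months: 1 − 0.95^3 = 14.3% and 1 − 0.975^3 = 7.3%.
- Both constructs must succeed, each on any of its own tests (three for functioning, four for activity). With no true effect: 0.073 × 0.096 = 0.7% favourable. If functioning truly improves and is always detected, the false claim rests on activity alone: 9.6%. In the reverse case it is 7.3%.

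**The case against.** Five arguments deserve an answer.

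1. *The hypothesis joins activity and functioning with an 'and', so both may be required.* This stands as a possible reading. With no true effect it brings the favourable error down to about 0.7%. But the article does not state such a rule. Even under it, the instrument and visit that count for each construct stay open, and the error rises to between 7% and 10% when only one construct truly improves.
2. *Short-term and long-term effects are separate questions and need not share one error budget.* This is a legitimate judgement. It lowers the figures to 9.6% and 7.3% in the favourable direction, still three to four times 2.5%.
3. *Some priority is implied.* The sample size rests on functioning, and the objective instruments are introduced as additional. This hints at an order, but it is not stated as an order of testing, and it does not settle instrument or visit.
4. *A separate analysis plan may hold the multiplicity rule.* It may, and mere silence in an article would be no finding. Here, however, the article gives four instruments equal primary status and states one unadjusted threshold for all analyses. A later plan that ranked or adjusted would have to override that statement.
5. *Combining self-report with objective measurement is a deliberate strength.* Agreed. All of these measures can be kept and reported. The issue is which of them decides.

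A reader might also infer that the chance of wrongly declaring e-Exercise effective is 24–30%. The documents do not support this. Figures of that size count significant differences in both directions, and a result favouring usual care cannot support a claim that e-Exercise is better. Nor does the article say that any one positive result suffices. That reading is only left open.

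**Conclusion.** The point holds in this form: seven primary contrasts, all at two-sided 0.05, with no hierarchy, adjustment or success rule in the article. If any single positive result may support the hypothesis, the chance of at least one false difference in either direction is 30% with independent tests and about 21–28% under the assumed correlations. The chance of a false result favouring e-Exercise is 16% and about 11–14% respectively, roughly four to six and a half times the 2.5% of a single two-sided test.

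Three conditions apply. The correlations are assumed, so the lower ends are illustrations and not bounds. The any-one-of-seven reading is neither stated nor excluded. All figures describe the case of no true effect on any measure. The documents also do not settle which instrument or visit should come first: the sample size names only the construct, and the research question gives 3 and 12 months equal standing. That choice is the sponsor's.

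**What to change.** Before unblinding, the sponsor should amend the plan in one of two ways.

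- **One primary endpoint.** Name one instrument and one time point for physical functioning, the construct behind the sample size. HOOS/KOOS function is the natural candidate. Test it at two-sided 0.05, then take the remaining primary contrasts in a prespecified fixed sequence, each at 0.05 only if the one before it was significant.
- **Two co-primary endpoints.** If physical activity keeps its status, name one instrument and one time point for each construct and apply Holm over those two tests.

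Measures and time points outside the chosen set are reported as secondary, with confidence intervals. The general threshold sentence should be reworded to match.

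Either route holds the family-wise error at 5% and needs no new data. According to the Blinding section the researchers stay blinded until the analyses are complete, and the Timeline puts the start of analysis in January 2016, so there is room to do this.

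The downside is that fewer results can be called confirmatory. Holm also costs some power, because its first step requires p ≤ 0.025. With n per arm = 2(z for alpha + 0.842)²/d² at d = 0.4 and 80% power, before loss to follow-up and clustering, a test at 0.05 needs 2 × 1.960-based 99 = 198 patients, and a test at 0.025 (z = 2.241) needs 2 × 119 = 238.

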#### Effectiveness

To determine the short (baseline-3 months) and long term (baseline −12 months) effectiveness of e-Exercise on primary and secondary outcomes, multi-level modelling of repeated measures will be performed controlling for baseline values and relevant confounders such as age, OA location and gender. With multilevel modelling of repeated measures it is possible to correct on one side for dependency of observations within subjects and, on the other side, to take into account the variation between physical therapists [50, 51]. The three-level hierarchy will exist of repeated measurements (level 1), nested within patients (level 2), nested within physical therapists (level 3).

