**RCT study procedures.**

### Participants

#### Physical therapists

A stratified random sample of 800 physical therapy practices in three provinces of the Netherlands (e.g. Noord-Holland, Utrecht and Gelderland) will be invited by letter to participate in the study. Contact information of physical therapy practices will be obtained from the national database for physical therapists of the Netherlands Institute for Health Services Research (NIVEL). Additionally, a recruitment advertisement will be placed in the online newsletter of The Royal Dutch Society for Physical Therapy (KNGF). Each participating physical therapy practice will be asked to enroll one or two physical therapists. The researchers will recruit 100 physical therapists. Inclusion criteria for physical therapists will concern: (i) practicing in primary care, (ii) treating at least six patients with OA of the hip and/or knee each year. Physical therapists practicing in another physical therapy practice participating in the study will be excluded.

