#### Patients

In order to include 200 participants, each physical therapist is requested to recruit about two patients. Since the study of Veenhof et al. [27] showed that recruitment of OA patients in the physical therapy practice is difficult and research has shown that different recruitment strategies do not affect treatment outcomes [28], this study uses various recruitment strategies. First, patients with hip and/or knee OA who visit a physical therapy practice will be invited to participate in the study. Second, recruitment advertisements will be placed in local newspapers. Third, information letters and flyers will be sent to general practitioners. Responders to these articles and flyers will be allocated to the nearest participating physical therapist. Eligibility criteria of patients interested in the study concern: (i) age 40–80 years, (ii) OA of the hip and/or knee according to the clinical criteria of the American College of Rheumatology (ACR) [29]. Exclusion criteria will include: (i) being on a waiting list for a hip or knee replacement surgery, (ii) being contra-indicated for PA without supervision, (iii) being sufficiently physically active according to the physical therapist, (iv) participation in a physical therapy and/or PA program in the last six months, (v) no access to internet, (vi) inability to understand the Dutch language. The diagnostic ACR clinical criteria for knee OA are: knee pain and at least three of the following six criteria: age > 50 years, morning stiffness <30 minutes, crepitation, bony tenderness, bony enlargement and no palpable warmth. Diagnostic ACR clinical criteria for hip OA are: hip pain and hip internal rotation < 15 degree and hip flexion ≤ 115 degree; or hip internal rotation ≥ 15 degree and pain on hip internal rotation and morning stiffness of the hip ≤ 60 minutes and age > 50 years [29]. Contra-indications for PA will be determined using the adapted Physical Activity Readiness Questionnaire (PAR-Q) [30]. This questionnaire is used to identify patients for whom PA is inappropriate.

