### Study procedure

Physical therapists willing to participate in the study will be screened on in- and exclusion criteria by a researcher (CK). Cluster randomization will be performed at the level of the participating physical therapy practices that will randomly be assigned to the intervention (e-Exercise) or the control group (usual care) by means of a computer-generated random sequence table. Physical therapists will receive a half day training about e-Exercise and the study procedure (intervention group) or about practicing according to the “KNGF guideline OA hip-knee” [10] and the study procedure (control group). Physical therapists will inform eligible patients about the study and screen them on in- and exclusion criteria. All suitable patients will be stimulated to contact the research team by telephone, e-mail or reply card. After an informative phone call with one of the researchers (CK or DB), interested patients will receive a letter about the trial and a request to complete an informed consent form. Patients recruited by the additional recruitment strategies (i.e. advertisements in newspapers and flyers from the general practitioner) will be informed by the researchers before they visit their physical therapist. Physical therapists in both groups will be asked to record the content of their treatment on a registration form. During the study period, both patient groups will continue their medication and usual care managed by other caregivers.

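### Practices are randomised but the effect model stops at the therapist, so standard errors may be too small if outcomes correlate across therapists within a practice

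*Protocol article*

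**What the plan says.** Under Study procedure, the protocol article sets the unit of randomisation: "Cluster randomization will be performed at the level of the participating physical therapy practices".

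Under Participants, Physical therapists, it sets how many therapists a practice may contribute: "Each participating physical therapy practice will be asked to enroll one or two physical therapists". The total is fixed there as well: "The researchers will recruit 100 physical therapists". Under Patients, "each physical therapist is requested to recruit about two patients".

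Under Statistical analysis, Effectiveness, the model for all primary and secondary outcomes is a three-level one, with measurements "nested within patients (level 2), nested within physical therapists (level 3"). One of its stated purposes is "to take into account the variation between physical therapists". The article mentions no practice level and no practice-clustered standard error.

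**The concern.** In a cluster randomised trial the analysis has to allow for correlation within the unit that was randomised. Here that unit is the practice, and the stated hierarchy ends one step below it. Where a practice supplies one therapist, therapist and practice are the same cluster and nothing is lost. Where it supplies two, both therapists are in the same arm by design, and the model counts them as two independent clusters.

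The therapist intercept does pick up correlation among patients of the same therapist, whether it arises at therapist or at practice level. What it cannot represent is correlation between patients of one therapist and patients of a colleague in the same practice. The article's own recruitment plan gives one possible source: responders to newspaper advertisements and general practitioner flyers are sent to the nearest participating therapist, so two therapists in one practice would draw on the same area.

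At stake is the nominal error rate. If such correlation exists, confidence intervals are too narrow and p-values too small, by the same mechanism at 3 and at 12 months and for every outcome that shows it.

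**Working it through.** **Inputs from the protocol article.** Randomised unit: practice. Therapists: 100, one or two per practice, hence between 100/2 = 50 and 100/1 = 100 practices. Patients per therapist: m = 2. Test: "at a 2-sided significance level of 0.05". Loss to follow-up: at most 20% of 200 patients.

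**Assumptions.** The Sample size section gives "power 0.8; alpha 0.05" but no ICC or design effect, so there is no clustering figure to reproduce. Let:
- ρp be the correlation, after covariate adjustment, between patients of different therapists in one practice, taken as 0.01 to 0.10;
- ρt be any further correlation among patients of the same therapist, first set to 0;
- f be the share of therapists who work in two-therapist practices.

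Cluster sizes are taken as equal, and the contrast is considered at a single time point.

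**Formulas.** These are variance factors relative to independent patients.
- Therapist-level model: V_model = 1 + (m − 1)(ρp + ρt)
- True, with practices randomised: V_true = V_model + f·m·ρp
- SE ratio: r = √(V_model / V_true)
- Actual two-sided alpha = 2[1 − Φ(1.96·r)]

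With f = 0 or ρp = 0 the extra term vanishes, r = 1 and alpha is the planned 0.05.

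**Worked case** (m = 2, f = 1, ρp = 0.05). V_model = 1 + 1 × 0.05 = 1.05. V_true = 1.05 + 1 × 2 × 0.05 = 1.15. r = √(1.05/1.15) = 0.956. Alpha = 2[1 − Φ(1.96 × 0.956)] = 0.061.

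**All cases, m = 2, ρt = 0.**

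| ρp | V_model | V_true, f = 1 | r | alpha | V_true, f = 0.5 | r | alpha |
|---|---|---|---|---|---|---|---|
| 0.01 | 1.010 | 1.030 | 0.990 | 0.052 | 1.020 | 0.995 | 0.051 |
| 0.02 | 1.020 | 1.060 | 0.981 | 0.055 | 1.040 | 0.990 | 0.052 |
| 0.05 | 1.050 | 1.150 | 0.956 | 0.061 | 1.100 | 0.977 | 0.056 |
| 0.10 | 1.100 | 1.300 | 0.920 | 0.071 | 1.200 | 0.957 | 0.061 |

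**Sensitivity.**
- *Extra therapist correlation.* With ρt = 0.05, no alpha in the table moves by more than 0.001.
- *Attrition.* With 20% loss, 160 patients over 100 therapists give m = 1.6. Alpha for ρp = 0.01 / 0.02 / 0.05 / 0.10 becomes 0.0518 / 0.0536 / 0.0590 / 0.0677 for f = 1, and 0.0509 / 0.0518 / 0.0545 / 0.0588 for f = 0.5.
- *Uneven recruitment.* If therapists in two-therapist practices recruited four patients each (assumed; f = 1, ρp = 0.05), V_model = 1 + 3 × 0.05 = 1.15, V_true = 1.15 + 4 × 0.05 = 1.35 and alpha is about 0.070.

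**Simulation check.** This used 40,000 trials per setting, with 50 practices, two therapists each and two patients each. The therapist-level analysis rejected a true null in 4.9% / 5.3% / 6.1% / 7.4% of trials at ρp = 0.01 / 0.02 / 0.05 / 0.10. An analysis of practice means rejected in 4.9% to 5.2%. This agrees with the formulas, and at ρp = 0.01 it shows no inflation at all.

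**The case against.** The strongest reply is that the loss is conditional and probably small. The documents give no ICC. If clustering sits with the therapist, which is the level the plan models, the bias is nil. The model adjusts for baseline values, age, OA location and gender, so only residual practice correlation counts, and part of any catchment difference will already have been removed. Practices hold about four patients at most, some will have a single therapist, and attrition shrinks clusters further. All of this stands. It limits the size of the problem but does not put the randomised unit into the model.

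Two further defences are weaker. An analysis plan might settle the hierarchy, but the article does not leave it open: it names each level, and the top one is not the unit randomised. The eligibility rule about therapists who work in another participating practice keeps one therapist from belonging to two study practices; it does not limit a practice to one therapist.

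A reader might also infer something stronger: that standard errors are too small for every outcome, or that all between-practice variation passes unmodelled into the treatment contrast. The documents support neither. The first needs a positive practice-level correlation that they do not report. The second overlooks that the therapist intercept already carries the part shared by patients of one therapist; only the covariance between two therapists of the same practice is lost.

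**Conclusion.** The mismatch between randomisation and model is certain from the text. Its effect is conditional: the standard error is too small only if outcomes correlate across therapists within a practice after adjustment, and only through two-therapist practices.

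Under assumed practice-level ICCs of 0.01 to 0.10 and two patients per therapist, actual alpha runs from about 0.052 to 0.071 if all practices supply two therapists, and from about 0.051 to 0.061 if half of the therapists work in such practices. The value 0.071 should not be read as the expected error rate: it needs the highest assumed ICC and two therapists in every practice. The treatment estimate itself is not materially biased. This should be fixed before analysis, but it does not undermine the trial.

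**What to change.** In Statistical analysis, Effectiveness, make practice the top level: repeated measurements within patients within practices, with therapist as an optional level in between if its variance can be estimated. With at most two therapists per practice and about two patients each, it may not be estimable. Keeping the present hierarchy and using standard errors clustered on practice would also serve.

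Degrees of freedom based on the number of practices are consistent with this but change little: with 50 practices the critical value on 48 degrees of freedom is about 2.01 instead of 1.96.

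The cost is one sentence. Practices were the units allocated, so their identifier is already held. Confidence intervals widen only as far as practice correlation requires: with two-therapist practices throughout, by 1/0.990, about 1%, at ICC 0.01, and by 1/0.920, about 9%, at ICC 0.10. The Timeline section places the start of analysis in January 2016 and the Blinding section keeps researchers blinded until analysis is complete, so the change can be made before any results by arm are known.
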